#### Patients

3.2.3

From the randomly selected nursing records, four patients per ward will be included (*N = *24) to participate in interviews and clinical observations. The inclusion criteria are patients older than 18 years, physically and mentally capable to take part in the interview (e.g. without serious symptoms and completely oriented) and being able to answer interview questions in the main national language.

### Study intervention

3.3

Guided clinical reasoning will be applied to the experimental group on GCR training days. The intervention comprises four single days at a duration of 5 months, and each GCR day comprises 7 hr. The participating nurses will receive materials on the Advanced Nursing Process including presentations, information about relevant websites, assigned reading and work assignments (Table 2). These documents will be distributed in printed form or as PDF files. Prior to starting GCR, the participating nurses will be asked about their previous knowledge, experiences, learning needs and interests. On each of the four GCR training days, several learning methods will be applied such as a GCR case‐meeting, presentations, small‐group work and discussion rounds. Additional work assignments (transfer tasks) to put the newly gained knowledge into clinical practice include formulating and documenting SNL‐based, accurate nursing diagnoses for a patient in the PES format (problem definition, aetiological factors and signs/symptoms) and writing coherent care plans. Verifying nursing diagnoses and the care plan with the patient is strongly recommended.

**Table 2 nop2299-tbl-0002:** Standardized educational intervention protocol GCR

Date	Objectives/contents	Assigned reading
Day 1	Advanced Nursing Process and nursing diagnoses (objectives, purpose, advantages and disadvantages, terms/definitions/concepts, references to nursing science, historical background, prospects, frequent nursing diagnoses, components of nursing diagnoses—PES format) Diagnostic process (steps, exercises, difficulties) NANDA‐I Taxonomy II (application of the work by Doenges et al. (2014)	History of the nursing process Clinical decision‐making in the diagnostic process by means of case‐meeting GCR Nursing process for leaders
Day 2	Reflections on assigned readings and examination of work assignments Exploration/definition of concepts (e.g. Advanced Nursing Process and nursing diagnostics) Problem areas in practical implementation Repetition of nursing diagnostic steps and clinical decision‐making Historical background and prospects NANDA‐I Taxonomy II (application of the work by Doenges et al. (2014)	Quality improvement by nursing diagnoses? Systematic review: nursing diagnoses, interventions and outcomes—application and impact on nursing practice Evaluation study relating to the implementation of nursing diagnoses, interventions and outcomes
Day 3	Reflections on assigned readings and examination of work assignments Reflecting economization and practice Diagnostic process: components of critical thinking, clinical decision‐making and difficulties Stating, validating and prioritizing nursing diagnoses	NNN‐nursing assessment Implementation project regarding electronic assessment Repetition of the first handout is recommended for evaluation Optional articles on critical thinking, GCR and electronic documentation
Day 4	Reflections on assigned readings and the work assignments Exercises relating to nursing diagnostic steps and application of the work by Doenges et al. (2014) Stating, validating and prioritizing nursing diagnoses Intervention study of nursing diagnoses, interventions and outcomes Repetition and conclusions	

In addition to the GCR training days, all nurses in the experimental group will participate in short GCR case meetings (0.5 hr) on their wards. All available nurses on duty (on average, eight persons) participate in these meetings, where one nurse acts as the case presenter. While GCR trainings will take place in a seminar room of the hospital, short GCR case meetings will be conducted in the field of work, that is, on the wards. GCR case meetings will be conducted three to five times during the nurses’ dayshift on the experimental wards. On the control wards, the nurses will not participate in a training and the current introduced nursing process including NANDA‐I‐nursing diagnoses will be continued. The same number of regular case meetings will be performed for the same duration but without GCR.

An internationally experienced expert (RN, nurse pedagogue and nursing scientist) will perform the GCR intervention.

### Expected outcomes

3.4

The primary outcomes are the level of the nurses’ knowledge, the level of their attitude, satisfaction with GCR, the quality of nursing diagnoses, interventions and outcomes and the frequency and variety of NANDA‐I‐nursing diagnoses (Doenges et al., 2014; NANDA‐I, 2016). The secondary outcomes are nurses’ behaviour in the field of work (clinical performance of the Advanced Nursing Process evaluated by observations and by patient interviews) and mutual comparisons of all findings.

### Data collection

3.5

#### Instruments

3.5.1

##### Knowledge test

3.5.1.1

A knowledge test will be distributed to the experimental and control groups on the first and last GCR days. This test was previously developed for evaluating similar GCR training sessions. After minor adjustments and a pre‐test, it contains eleven items: six qualitative knowledge questions, two supplementary control questions on content not covered by the GCR sessions and three self‐evaluations on the learning success. For the knowledge items, the maximum attainable test score is 58 points, and for the control items, the maximum score is thirteen points. Participants take the test silently by hand under expert supervision. A maximum of 30 min is allowed for its completion and the participants fill in a personal four‐digit number (e.g. the last digits of their mobile phone) to code the test(s), thus allowing anonymous, matched comparisons before and after the GCR training.

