### Study design and setting

3.1

A complex experimental intervention study using data and method triangulation will be performed. A complex intervention contains a “number of interacting components […], number and difficulty of behaviours required by those delivering or receiving the intervention, number of groups or organizational levels targeted by the intervention, number and variability of outcomes [and] degree of flexibility or tailoring of the intervention permitted” (Craig et al., 2008). General teaching and learning processes as well as GCR are guided and influenced by teachers’ and participants’ behaviour and various context conditions. Furthermore, the knowledge transfer from the learning field to the work field including organizational influencing factors will be considered, and therefore, several outcomes on different levels will be measured. Quantitative methods will be used to take knowledge tests and self‐assessments on nurses’ attitude towards the Advanced Nursing Process. The quality of the Advanced Nursing Process—including the accuracy, frequency and variety of nursing diagnoses—will be evaluated by nursing record audits with the Q‐DIO R instrument. However, a general criticism is how the nursing reality is represented in the nursing records. Therefore, to the objectives of level 3 evaluation, observations of nurses’ clinical performance of the Advanced Nursing Process, interviews with patients and qualitative document analyses will be performed to verify the Q‐DIO results (Kirkpatrick & Kirkpatrick, 2008, 2010).

The study will be conducted in a Swiss public hospital. From a total of 12 wards, seven fulfil the inclusion criteria in that they are acute geriatric (2), internal medicine (3) or surgical (2) inpatient wards. By sealed‐envelope drawings, three wards will be randomly allocated to the experimental group, three to the control group and one will be excluded.

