#### Registered nurses

3.2.1

All RNs of the six included wards will be recruited (*N = *92) for attitude measurements. Using stratified convenience sampling, a third (*N = *34) of the RNs will participate as experimental group in GCR training (*N = *17) or as control group (*N = *17). Both groups should contain a similar grade‐skill mix of ward managers, nurse instructors, Advanced Nursing Process mentors and regular RNs. All ward managers will be included. The aim is to empower them for taking responsibility on the Advanced Nursing Process. As role models, their knowledge, attitude and behaviour should spread to their teams. The inclusion criteria are being in a leadership, teaching or clinical position, applying the Advanced Nursing Process and understanding the main national language.

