##### Positions on the Nursing Diagnoses Scale (PND)

3.5.1.2

The nurses’ attitude towards nursing diagnoses will be measured using the self‐assessment instrument PND (Lunney & Krenz, 1994), which contains 20 items with positive and negative pairs of bipolar attitude adjectives on a 7‐point Likert scale. The total score ranges from 20–140; the more positive the attitude, the higher the total score. The German PND version has been previously evaluated (Leoni‐Scheiber, Gothe, & Müller‐Staub, 2016). The psychometric properties of the original PND showed favourable results: its content validity exceeded an agreement of 90% by four expert raters (Lunney & Krenz, 1994), the test–retest reliability as measured by intraclass correlation coefficient was 0.90 (95% CI [0.87, 0.92]), and the internal consistency as measured by Cronbach's alpha coefficient was 0.96 (Romero‐Sánchez, Paloma‐Castro, et al., 2013). The construct validity was measured by confirmatory factor analysis and showed highly correlated factors in the three‐factor model solution (≥0.96) (D'Agostino et al., 2016). The PND requires 5 min to complete and will be filled out by the participating nurses in handwriting on the first and last GCR days and 3 months later on their respective wards. To assure anonymity and to ensure that the results can be compared with the knowledge tests of each nurse, the participants will be asked to fill in the same four‐digit number as in the other instrument.

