#### Measurement time points before and after the GCR study intervention

3.5.2

Data collection will occur at three time points; the flow chart in Figure 3 presents all data collection methods and time points. As baseline measurement before the GCR intervention (*t*0_1_ + *t*0_2, _illustrated in boxes): a sample of nursing records will be drawn, and nurses of the intervention and control group perform the knowledge tests and all nurses of the participating wards fill out the PND scales (illustrated in circles). After GCR, the participants complete knowledge tests and PNDs for the second time and complete the satisfaction survey (*t*1). After ending of the GCR intervention, all nurses complete the PND a second and a third time. At that time, a second sample of nursing records will be drawn. In addition, patient care will be observed (nurses’ clinical performance) and patients are interviewed to cross‐validate the Q‐DIO R results on the quality of the Advanced Nursing Process as described in the nursing records.

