### Ethical considerations

3.7

This study was authorized by the regional ethics committee in April 2016 (Nr. PB_2016_00990), and data collection has started. The study will be executed in conformity with the Declaration of Helsinki (WMA, 2013) and with Good clinical practices (Altpeter et al., 2005).

The nurses and the nursing director will be asked for voluntary participation. Nursing records from the archives (pre‐intervention data) were permitted to be retrieved without patients’ informed consent. Written informed consent will be obtained for postintervention document analyses, for patient observations and for interviews. Comprehensive written and oral information on the study aim and procedures, together with descriptions of the patients’ rights as study participants, will be provided at least 1 day before data collection.

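### The nurses' baseline knowledge test and attitude score are set for the first training day, after wards are allocated, and no safeguard is described for recruiting and selecting nurses from wards already drawn

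*Protocol article*

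**What the plan says.** All references are to the protocol article.

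- **Allocation (3.1).** Seven wards qualify. By sealed-envelope drawing, "three wards will be randomly allocated to the experimental group, three to the control group and one will be excluded".
- **Recruitment (3.2.1).** For attitude, "All RNs of the six included wards will be recruited" (92 nurses). From these, 34 are taken as 17 for training and 17 as controls: "Using stratified convenience sampling, a third". All ward managers are included.
- **Knowledge baseline (3.5.1.1).** "A knowledge test will be distributed to the experimental and control groups on the first and last GCR days".
- **Attitude baseline (3.5.1.2).** The PND "will be filled out by the participating nurses in handwriting on the first and last GCR days and 3 months later on their respective wards".
- **Definition of baseline (3.5.2).** Baseline means before the GCR intervention. The knowledge test is taken by nurses of the two named groups, and "all nurses of the participating wards fill out the PND scales".
- **Consent (3.7).** "The nurses and the nursing director will be asked for voluntary participation". No date relative to the draw is given. The same section says that data collection has started.
- **Analysis (3.6).** Wilcoxon tests compare time points, Friedman tests cover the three PND measurements, and Mann-Whitney tests compare arms. All are one-sided at 0.05.

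**The concern.** Sealed envelopes protect the draw of wards. They do not protect what happens afterwards to the people inside the wards: who agrees to take part, who is picked for the groups of 17, and how they answer the first questionnaire. In a trial randomised by ward, those steps are safe from the allocation only if they come before the arm is known.

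Here the article places the first measurement on the first training day, in groups that already carry their arm names. The PND is a self-rating of attitude. A nurse starting a four-day programme and a nurse on a ward that gets no training may answer it differently on the same day for reasons unrelated to any effect of the training. They may also differ in their willingness to fill it in. Knowledge and attitude are both primary outcomes (3.4) and make up the first hypothesis (2.4).

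**Working it through.** **Order of events, from the text**

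1. One drawing sorts seven wards into three experimental, three control and one excluded (3.1).
2. The six included wards exist as a set only once that drawing has removed the seventh. Section 3.2.1 describes the 92 nurses as coming from this set, and the 34 as chosen from them by convenience into two named groups.
3. The first knowledge test, and the participating nurses' first PND, fall on GCR day 1 (3.5.1.1, 3.5.1.2).
4. Section 3.5.2 places baseline before the intervention, not before allocation.

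So for these nurses the order is draw, then baseline, then training.

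**Who can know the arm at baseline**

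- The 17 trainees: certain by day 1, since they are attending the training.
- The 17 controls and the remaining 92 − 34 = 58 nurses: plausible, because arms are whole wards and control wards get no training (3.3). It is not stated.

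**Which tests are reached**

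- *Wilcoxon and Friedman (within group):* the baseline score enters directly, so any expectation shift at baseline enters the measured change.
- *Mann-Whitney (between arms):* section 3.6 compares scores and states no baseline adjustment. A shifted baseline score does not enter a comparison of post-training scores. Selective participation, or selection of the 34, does.
- *Record audit (Q-DIO R):* pre-intervention records come from the archives (3.7) and are unaffected.

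**Scale, under assumptions**

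The article gives no PND standard deviation, uptake rate or pre-post correlation. Its only sample-size calculation (3.2.2) concerns records. It reproduces: the one-sided unpaired t-test needs 31.9, 44.7 and 43.3 per group, which round up to the stated 32, 45 and 44. The present point does not depend on it.

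Assumed throughout: no GCR effect, one-sided 5%, t-tests standing in for the rank tests, clustering ignored, and an even 46/46 split of the 92 nurses.

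*Paired test, n = 46, correlation r, baseline shifted by δ SD.* The SD of the change is √(2(1 − r)), and the non-centrality is (δ / SD of change) × √n. With r = 0.7, the SD of the change is √0.6 = 0.775. For δ = 0.10, the non-centrality is (0.10 / 0.775) × √46 = 0.876.

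| Baseline shift | r | Rejection rate |
|---|---|---|
| 0.10 SD down | 0.5 | 16.4% |
| 0.10 SD down | 0.7 | 21.7% |
| 0.10 SD down | 0.9 | 44.0% |
| 0.10 SD up | 0.7 | 0.6% |

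*Two-sample test, arms differing by δ SD through uptake or selection alone.* The non-centrality is δ√(n/2). For n = 46 and δ = 0.10 it is 0.10 × √23 = 0.480.

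| δ favouring GCR | 46 v 46 | 17 v 17 |
|---|---|---|
| 0.05 SD | 8.0% | 6.7% |
| 0.10 SD | 12.1% | 8.7% |
| 0.20 SD | 24.4% | 14.1% |

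A difference favouring control pushes these rates below 5%: for 0.10 SD, 1.7% (46 v 46) and 2.7% (17 v 17).

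**The case against.** Several points against a stronger reading are right.

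- *A reader might infer that the draw was open and that all 92 nurses knew their arm when they agreed.* The text says sealed envelopes, gives no date for consent, and does not say when or to whom the result was disclosed. Naming the six included wards may simply describe the final sample; consent sought in all eligible wards before the draw would fit the same sentence. The study flow chart (Figure 3) is not shown. Only the trainees' knowledge on day 1 is certain.
- *A reader might infer that the error rate is inflated by a known amount.* It is not known. Nurses about to be trained could rate themselves up as easily as down, and an upward baseline shift makes the within-group test conservative.
- *A reader might infer that a tainted baseline biases every comparison.* It does not enter an unadjusted post-training Mann-Whitney test.
- *The room for bias is limited.* The PND is meant for every nurse on the six wards, so only refusal or non-response can select there. The knowledge test is supervised, timed and scored, with separate control questions; expectation can hardly create knowledge.
- *An article may leave the order of consent and draw to the full protocol.* That holds for consent. It does not hold for the baseline, which the article itself dates to the first GCR day in named groups.

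The stated timing of the baseline therefore stands, as does the lack of any described safeguard for recruitment and selection after the draw.

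**Conclusion.** The point holds in limited form. The knowledge baseline, and the PND baseline of the participating nurses, come before training but after allocation, and nurses are described as recruited and partly chosen by convenience from wards already drawn. They cannot be presented as pre-allocation values.

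The main exposure is the self-rated PND in the within-group tests. The between-arm tests are exposed only through who takes part or is picked. Direction and size cannot be determined from the article; the rates above show only that shifts of 0.05 to 0.20 SD would matter at these sample sizes, and they rest on the assumptions listed with them. Moving the baseline would not remove expectation that persists after training, because the training is visible to those who receive it.

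This is an inexpensive improvement to two primary outcomes. It does not show that the trial's result would be wrong.

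**What to change.** **If the baseline is still to come,** use the same envelopes in two steps:

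1. Draw the one ward to be excluded.
2. In the remaining six wards, name the 34 nurses, ask for participation, and collect the baseline PND from all nurses and the baseline knowledge test from the 34.
3. Only then open the envelopes that assign three wards to each arm.
4. Change sections 3.5.1.1 and 3.5.1.2 so that the first measurement is before the arm assignment and not on the first GCR day.

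No extra nurses or forms are needed: the 5-minute PND and the 30-minute test move to an earlier date. The downside is small. The first test no longer fits into training day 1, and there is less time after the draw to roster the trainees.

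**If the baseline has already been collected,** which section 3.7 makes possible, state that the t0₂ measurement followed allocation. Report PND participation by ward and arm at each time point, and rest the conclusion on the between-arm comparison, not on within-group change from t0₂. This costs only reporting.

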##### Positions on the Nursing Diagnoses Scale (PND)

3.5.1.2

The nurses’ attitude towards nursing diagnoses will be measured using the self‐assessment instrument PND (Lunney & Krenz, 1994), which contains 20 items with positive and negative pairs of bipolar attitude adjectives on a 7‐point Likert scale. The total score ranges from 20–140; the more positive the attitude, the higher the total score. The German PND version has been previously evaluated (Leoni‐Scheiber, Gothe, & Müller‐Staub, 2016). The psychometric properties of the original PND showed favourable results: its content validity exceeded an agreement of 90% by four expert raters (Lunney & Krenz, 1994), the test–retest reliability as measured by intraclass correlation coefficient was 0.90 (95% CI [0.87, 0.92]), and the internal consistency as measured by Cronbach's alpha coefficient was 0.96 (Romero‐Sánchez, Paloma‐Castro, et al., 2013). The construct validity was measured by confirmatory factor analysis and showed highly correlated factors in the three‐factor model solution (≥0.96) (D'Agostino et al., 2016). The PND requires 5 min to complete and will be filled out by the participating nurses in handwriting on the first and last GCR days and 3 months later on their respective wards. To assure anonymity and to ensure that the results can be compared with the knowledge tests of each nurse, the participants will be asked to fill in the same four‐digit number as in the other instrument.

##### Satisfaction survey

3.5.1.3

This survey will be applied to assess the participants’ satisfaction with GCR. It contains seven items with three‐ and four‐point scale answer options (e.g. very good, good and bad) and a bipolar eight‐point Likert scale with three pairs of opposite views (e.g. GCR content has practical relevance or is too theoretical). Additional free space allows adding comments to each item. This survey will be completed on the last GCR day by hand and requires 5–7 min for completion. The participants use the same personal four‐digit number as for the other instruments. To obtain insight into satisfaction with GCR from a leadership perspective, a semi‐structured interview with the nursing director will be conducted and recorded (Kirkpatrick & Kirkpatrick, 2010).

##### Clinical observation guide

3.5.1.4

The semi‐structured guide for nonparticipatory observations by four APNs covers four areas: patients’ central nursing problems that the nurses address, performed nursing interventions and the effectiveness of interventions in affecting nursing problems/diagnoses and nursing outcomes. The observations will be recorded by hand, and the observation duration ranges from 30–60 min and occurs on the same observation day.

